#### Exclusion criteria

Patients who meet any of the following criteria will be excluded:Patients with known central nervous system involvement by lymphoma that is not in remissionHistory of other malignancy within the last 2 years except for:Non-invasive malignancies, such as adequately treated ductal carcinoma in situ of the breast, non-melanoma skin cancer or lentigo maligna, cervical carcinoma in situ and urothelial papillary non-invasive carcinoma or carcinoma in situProstate intraepithelial neoplasia without evidence of prostate cancerReceiving (or within a month of) chemotherapy, immunotherapy or treatment with immunosuppressive agents. This includes any systemic steroids at a dose exceeding 10 mg prednisolone (or other steroid equivalent) within 2 weeks prior to the first dose of varlilumabSignificant concurrent, uncontrolled medical condition that, in the opinion of the investigator, contraindicates participation in this studyActive and documented autoimmune disease (including, but not limited to, inflammatory bowel disease, coeliac disease, haemolytic anaemia or immune thrombocytopenic purpura) prior to the first dose of varlilumabActive infection requiring systemic therapyWomen who are pregnant or lactatingSerological positivity for hepatitis B (HBV) or C, or known HIV infection. As per the standard of care, the results of hepatitis serology should be known prior to commencement of immunochemotherapyPositive test results for chronic HBV infection (defined as positive HBsAg serology and positive HBcAb). Occult or prior HBV infection (defined as negative HBsAg and positive HBcAb). Participants who have protective titres of hepatitis B surface antibody (HBsAb) after vaccination will be eligiblePositive test results for hepatitis C (antibody serology testing)Previous recipient of an allogeneic bone marrow transplant at any timeAutologous bone marrow transplant within 100 days of first dosingSystemic radiation therapy within 4 weeks or prior focal radiotherapy within 2 weeks prior to first dosingKnown or suspected of being unable to comply with the protocolOngoing toxic manifestations of previous treatments. Exceptions to this are alopecia or certain grade 1 toxicities that, in the opinion of the investigator, should not exclude the patientUncontrolled congestive cardiac failure, cardiac ischaemia or cardiac arrhythmia. Clinically significant cardiac disease including unstable angina, acute myocardial infarction within 6 months prior to registration or congestive heart failure (NYHA III–IV)Known hypersensitivity to rituximab (grade 3 or higher) or murine proteins, or any other excipients used in the formulation of rituximab

#### Withdrawal criteria

Participants are free to withdraw consent from the study at any time without providing a reason. A participant may also withdraw from receiving study treatment but may not wish to withdraw from the trial. In this instance, the participant will be encouraged to attend follow-up visits in accordance with the trial schedule. Should any participant become pregnant during the trial, study treatment will be discontinued.

### Study procedure

#### Recruitment and consent

Patients are approached within a hospital setting and screened for eligibility by research staff to ensure all inclusion and exclusion criteria are met. Informed consent to enter the trial is obtained from a patient by a clinician only after a full explanation has been given, a patient information sheet has been provided and time has been allowed for consideration. Patients may provide written consent up to 28 days prior to randomisation. Patients are also asked to consent to provision of tumour and blood samples for use in laboratory studies, including genetic analysis, and to consent to their data being shared anonymously to support other research in the future (see Additional file 2).

#### Baseline visit

Following informed consent, assessments including a physical examination; full blood count; direct antiglobulin test; serum biochemistry, including renal, liver and bone profiles; creatinine clearance; immunoglobulins and paraprotein estimation; beta-2 microglobulin; serum lactate dehydrogenase; thyroid function test; serology (hepatitis B or C and HIV) and an electrocardiogram are completed within 28 days prior to treatment commencing, with disease evaluation being undertaken through contrast-enhanced computed tomography or PET-CT (positron emission tomography–computed tomography) in accordance with local policy and routine practice for the relevant disease site. Concomitant medications, ECOG performance status and medical history will be recorded within 14 days of treatment. In addition, women of childbearing potential will undertake a pregnancy test within 14 days. Following registration, fresh tumour tissue will be obtained through a needle biopsy for translational work (Fig. 3). Randomisation will occur 72 h prior to treatment start and where necessary, a further full blood count, serum biochemistry and ECOG performance status will be assessed (Fig. 4).

**Fig. 3 Fig3:**
[figure not shown]
Overview of translational samples. C*x*D*x*: Cycle *x* Day *x*, EOT end of trial, FU follow-up, PK pharmacokinetics, SCR screening

**Fig. 4 Fig4:**
[figure not shown]
Screening and randomisation. CT computed tomography, ECG electrocardiogram, Exc exclusion, Hep hepatitis, HIV human immunodeficiency virus, Inc inclusion, PET positron emission tomography

#### Treatment and follow-up visits

Participants attend hospital appointments for treatment cycles with assessments as per the baseline visit plus assessments of AEs, blood samples for translational analyses and pharmacokinetics (Fig. 3) and treatment compliance. Following the treatment, participants will attend post-treatment and progression follow-up visits where data will be collected on AEs, disease status and survival status (Figs. 5 and 6). Serious adverse events (SAEs) will be reported in real time to the SCTU pharmacovigilance team throughout the study. SAEs are assessed to determine whether they are related to drug treatment and whether they were unexpected. SAEs are subsequently reported to both Celldex, who are one of the manufacturers of varlilumab and who provide it for this trial, and the appropriate UK regulatory bodies.

**Fig. 5 Fig5:**
[figure not shown]
Assessments during treatment and administration of treatment (cycle 1). PK pharmacokinetics

**Fig. 6 Fig6:**
[figure not shown]
Assessments during treatment (cycles 2–6), at end of treatment and at follow-up (arms A and B), and administration of treatment. CT computed tomography, PK pharmacokinetics, PET positron emission tomography

### Data collection

Research staff at hospitals will complete trial electronic case report forms via a remote data collection tool (Medidata Rave). Data will be checked for missing or unusual values and checked for consistency within participants over time by SCTU trial staff. Any inconsistencies in data will be raised as data queries with the relevant site. Site staff will respond to such queries to provide an explanation or resolution of the discrepancies. Full details of the data management procedures are available in the RIVA data management plan, available on request.

### Source document verification and monitoring

The trial will be monitored and audited in accordance with SCTU procedures. In stage 1, every time a patient is registered, a monitor from the SCTU will visit the site to verify the source data. This monitoring will encompass comparing entries on the trial electronic case report forms with patients’ medical records and other supporting documents at the site and documented in the monitoring report form. Details will remain confidential, consistent with data protection regulations. Drug accountability will also be monitored throughout the trial. In stage 2, the SCTU will use a risk-based monitoring process to determine monitoring frequency and extent.

### Sample size

If fewer than 13% of the participants respond to the treatment, then this combination would be deemed insufficiently active to warrant further study. If, however, 40% or more of the participants respond to the treatment then the combination would be deemed worthy of further investigation. Using a one-stage Fleming design at α = 0.05 (one-sided) and 90% power, this would require 20 participants in each of the high- and low-grade arms (arms A and B combined). If during the safety phase one of the treatment arms is closed, then all participants will be recruited to the remaining arm so that the total sample size is 20 in each disease category. A total of 40 participants will be recruited, with 20 participants in each of the following subcategories:High-grade lymphoma (DLBCL, FL grade 3b or transformed FL) (*n* = 20)Low-grade lymphoma (e.g. FL grade 1, 2 or 3a, marginal zone lymphoma or mantle cell lymphoma) (*n* = 20)

The decision on whether there is sufficient activity to warrant further investigation in a future phase III will based on the following criteria:Within each of the high-grade and low-grade subcategories, if six or more out of the 20 participants respond to treatment.There is increased intratumoural B-cell depletion in the day 8 biopsies of participants who have received rituximab and varlilumab compared to rituximab alone.There is increased activation or an increase in the absolute numbers or proportions of macrophages, monocytes or neutrophils in the day 8 tumour biopsies of participants who have received rituximab and varlilumab compared to rituximab alone.

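### The rule of 6 or more responders in 20 has exact power 87.4% at a 40% response rate, slightly below the stated 90%; n and cut-off can stay, the figure should be restated

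*Protocol article*

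**What the plan says.** All the inputs are in the Sample size section of the protocol article.

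- **Unacceptable rate:** "If fewer than 13% of the participants respond to the treatment, then this combination would be deemed insufficiently active".
- **Target rate:** "40% or more of the participants respond to the treatment then the combination would be deemed worthy of further investigation".
- **Method and error rates:** "Using a one-stage Fleming design at α = 0.05 (one-sided) and 90% power".
- **Sample size:** "and 90% power, this would require 20 participants in each of the high- and low-grade arms", with arms A and B pooled, so 40 in total.
- **Response criterion:** "Within each of the high-grade and low-grade subcategories, if six or more out of the 20 participants respond to treatment".

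The same list adds two laboratory criteria from the day 8 biopsies, one on B-cell depletion and one on myeloid cells. The Statistical analysis section (Stage 2) pools the two arms and reports the response percentage with a 90% confidence interval for the low-grade and the high-grade group. Power is stated for each grade only. The article does not say whether the 90% is an approximate or an exact figure.

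**The concern.** The sample size is justified by one calculation and the decision is taken by another. Fleming's formula treats the response proportion as continuous, whereas the decision depends on a whole number of responders. With only 20 participants, moving to the next whole number can shift power by several points, so a power from the formula need not be the power of the printed rule.

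What is at stake is the risk of setting aside an active combination. A reader who sees 90% power takes the chance of missing a true 40% response rate to be 10% in each grade. Anyone weighing a result of 5 responders in 20 needs the error rate of the rule itself.

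**Working it through.** **Inputs** (Sample size section): p0 = 0.13, p1 = 0.40, one-sided alpha = 0.05 (z = 1.645), power 0.90 (z = 1.2816), n = 20 per grade, pass if X ≥ 6.

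**Step 1. Reproduce the plan's n by the method it names.**

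n = [(z_alpha·√(p0·q0) + z_beta·√(p1·q1)) / (p1 − p0)]²

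= [(1.645·√(0.13·0.87) + 1.2816·√(0.40·0.60)) / 0.27]²

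= [(0.553 + 0.628) / 0.27]² = 19.13, rounded up to 20. This agrees with the plan.

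**Step 2. Reproduce the cut-off.**

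n·p0 + z_alpha·√(n·p0·q0) = 2.60 + 1.645·√(20·0.13·0.87) = 5.07. The first whole number above this is 6. This agrees with the plan.

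**Step 3. Approximate power at n = 20.**

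Φ[(0.27·√20 − 0.553) / √0.24] = Φ(1.336) = 90.9%. The stated 90% is therefore what the named method gives.

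**Step 4. Exact operating characteristics of the count rule.** With X binomial(20, p):

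| Pass if | Type I error, p = 0.13 | Power, p = 0.40 |
|---|---|---|
| X ≥ 5 | 10.8% | 94.9% |
| X ≥ 6 (the plan's rule) | 3.7% | 87.4% |
| X ≥ 7 | 1.0% | 75.0% |

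A lower cut-off breaks the alpha limit and a higher one loses more power. No cut-off at n = 20 satisfies both stated figures.

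**Step 5. Where the gap comes from.** The approximation places the boundary at 5.07, but a count cannot pass until it reaches 6. With the boundary at the continuity-corrected value of 5.5, the normal calculation gives 1 − Φ[(5.5 − 8)/√4.8] = 87.3%, close to the exact 87.4%. Discreteness accounts for the gap.

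**Step 6. Size of the gap.**

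- Power: 90 − 87.4 = 2.6 percentage points. The false-negative risk at 40% is 12.6% instead of 10%.
- The rule reaches 90% exact power at a true response rate of 41.5%.
- The smallest exact design that meets both stated figures is n = 21 with the same cut-off of 6 (type I error 4.6%, power 90.4%), one more participant per grade.

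**Step 7. Joint figure, conditional only.** If both grades had to pass, were independent, and each had a true rate of exactly 40%, the probability would be 0.8744² = 76.5%.

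**The case against.** The strongest reply is that nothing was miscalculated. The protocol names Fleming's design, and that method returns its n, its cut-off and about 90.9% power. It never calls the 90% exact. The shortfall amounts to one participant per grade, and the exact type I error of 3.7% is tighter than the 5% allowed. The trial is a phase IIa study that reports estimates with 90% confidence intervals and makes no formal comparisons between groups.

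Most of this stands: the sample size is soundly derived, and the point is not a sample-size error. It does not settle the matter, because the approximation explains where the 90% came from without making it true of the rule that will decide the outcome. The exact figure is easy to compute and can be quoted instead.

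A reader might also infer that the trial has only about 76% power, because the criterion applies within each of the two grades. The documents do not support that as a shortfall. Each grade is sized and reported on its own, no joint power is claimed, and the text does not clearly require both grades to pass. A reader might equally take 87.4% as the chance of a decision to proceed. It is not, because the two biopsy criteria also enter that decision and no power is given for them.

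**Conclusion.** The point holds as a minor correction. For the printed rule, exact power at a 40% response rate is 87.4% per grade rather than 90%, and exact one-sided type I error at 13% is 3.7%. These figures assume 20 participants counted in each grade, independent responses, and a common true response rate across the pooled arms within a grade. They describe the response criterion alone. The wording on the two grades would also benefit from one clarifying sentence, since the protocol leaves a both-must-pass reading open.

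**What to change.** In the Sample size section, replace the claim of 90% power with wording such as: *With 20 participants per grade and a threshold of 6 or more responders, the exact one-sided type I error is 3.7% at a 13% response rate and the exact power is 87.4% at 40%, for each grade separately.* Keep the reference to Fleming's design as the source of n = 20.

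Add one sentence stating that the response criterion is judged separately in each grade. Only if the sponsor intends that both grades must pass should it say so and quote the joint power of about 76%, with its assumptions of independent grades and a true rate of 40% in each.

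The cost is two sentences. No extra participants are needed and the threshold does not change; the quoted power becomes slightly less favourable. If the sponsor prefers to keep a 90% claim that is exactly true, 21 per grade with the same cut-off would do it, at two more participants in total (42 instead of 40), but the correction does not require this.

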### Statistical analysis

#### Stage 1

All patients entered into stage 1 will be accounted for. The analysis will focus on the incidence of DLT, which will be summarised by treatment arm (and within the high-and low-grade subtypes). In addition, baseline characteristics, details of dose delivery and all toxicities on the CTCAE toxicity scale (version 4.03) during treatment will be summarised by grade and dose cohort. Details of dose delivery will also be summarised.

#### Stage 2

The analysis will be conducted for the intention-to-treat population, which includes all randomised patients who have commenced study treatment. We do not expect a difference in response rates by arm, so for analyses, participants from arm A and arm B will be combined. There will be no formal statistical comparisons between groups, and any *p* values presented will be exploratory (the main purpose for having two experimental treatment arms is to provide a comparator for the translational endpoints, i.e. to assess whether the differences observed are due to the addition of varlilumab to rituximab). For the primary endpoint of response, the percentage of responders and the 90% confidence interval will be presented for both the low- and high-grade groups. For other descriptive categorical data, proportions with a 90% confidence interval will be presented and for continuous data, means and a 90% confidence interval will be presented (or median and interquartile range if appropriate). For time-to-event data, Kaplan–Meier curves and waterfall plots for the response endpoint will be presented. A statistical analysis plan will be developed for the interim analysis and the final analysis.

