#### Stage 1 – safety

During the safety phase, six participants (three from each arm and from any subtype) will be treated. The number of DLTs experienced by these participants in each arm after having completed the first cycle will dictate whether we proceed to the second stage of the trial.

The options are as follows (Fig. 2):In each arm, if none of the three participants experience DLT, then we will proceed to stage 2.In each arm, if one or two out of three participants experience DLT, then we will expand the cohort to three more participants.If at most one or two out of the six participants experience DLT, we will proceed to stage 2.If three or more out of the six participants experience DLT, recruitment for that arm will be stopped.If all three of these participants experience DLT, recruitment for that arm will be stopped.

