#### Definition of DLT

DLT, measured using CTCAE, version 4.03, is defined as a highly probable or probable treatment-related AE that occurs between the first dose of varlilumab and day 1 of the second cycle of treatment. Specifically, the relevant AEs are:Grade 4 neutropenia >7 days’ duration despite treatment with granulocyte-colony stimulating factor (G-CSF)Febrile neutropenia (fever of unknown origin without clinically or microbiologically documented infection) with grade 3 or 4 neutropenia (absolute neutrophil count, ANC < 1.0 × 10^9^/L and fever > 38.5 °C)Thrombocytopenia grade 4 for > 5 days or associated with active bleeding despite supportGrade 3 or 4 cytokine release syndrome or infusion-related reactions despite pre-medicationGrade 3 or 4 non-haematological toxicity, including grade 3 and 4 biochemical AEsEvent with a fatal outcome

AEs that are not relevant for DLT include:Grade 3 nausea or grade 3 or 4 vomiting in participants who have not received optimal treatment with anti-emeticsGrade 3/4 diarrhoea in participants who have not received optimal treatment with antidiarrhoealsLymphopenia

Initially, the first patient will be entered into the trial, providing there are no serious or unexplained safety issues during cycle 1, as determined by the safety review committee (SRC). The dosing of subsequent participants will continue as they are identified. Should toxicity findings of concern occur, the SRC may choose to stagger the start of dosing for subsequent participants and/or cohorts. Recruitment was paused after the first participant was registered. At the first SRC meeting, the members of the committee agreed that recruitment need not be paused while waiting for the second SRC meeting to take place.

 Depending on the tolerability of the combination, the number of patients recruited into stage 1 of the trial will range from 6 to 12.

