#### Stage 2 – activity, safety and feasibility

The objective of stage 2 is to obtain further information on the safety of the intervention in a larger sample, information on activity (response rate overall and per lymphoma subtype) and the feasibility of administrating rituximab and varlilumab together. During stage 2, recruitment will continue until there is a total of 10 participants per arm and per grade (low/high). Including those recruited in stage 1, there will be a total of 20 participants per grade, and 40 participants in the trial in total. The main purpose for having two experimental treatment arms is to provide a comparator for the translational endpoints, i.e. to assess whether the differences observed are due to the addition of varlilumab to rituximab.

In both stages, no dose reductions are allowed for rituximab or varlilumab, but treatment may be interrupted or discontinued, or the infusion rate may be changed, at the discretion of the investigator for severe infusion or allergic reactions, or other toxicities. Guidelines on the management of infusion-related reactions are provided in Additional file 1.

A new cycle of treatment can be administered to a participant if the following conditions are met:ANC ≥1.0 × 10^9^/L (or not lower than ANC at screening). G-CSF support is permitted at the investigator’s discretion.Platelets ≥75 × 10^9^/L (or not lower than platelet count at screening). This platelet count must not be supported by platelet transfusions.Severity of non-haematological toxicity reduced to grade 1 or less (or grade 2 or less at the investigator’s discretion, if not considered a safety risk). Further guidance on the management of non-haematological toxicity is available on request.

The administration of rituximab and varlilumab must be delayed by 1 week if these conditions are not met. If toxicities have not improved to the limits described above, treatment may be delayed by a further week. Initiation of the next cycle can be delayed by a maximum of 3 weeks. Thereafter, if the toxicity has not improved to the limits above, treatment according to the trial protocol will be permanently discontinued for that participant.

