To validate our preclinical observations, pre- and post-treatment biopsies will be performed to monitor the level of B-cell depletion and the composition of other immune cell subsets. A comparator arm with rituximab alone would have been ideal, but this would not be an effective treatment option in this population. The only difference between arms A and B is the variation in the timing of the administration of varlilumab in cycle 1. This enables the collection of a post-treatment biopsy from patients who have received rituximab only and those who have received both rituximab and varlilumab, thus allowing a biological comparison of the effects of varlilumab alone. If these two experimental arms are shown to be active and safe, then a future randomised phase trial comparing the combination against a control arm will be undertaken.

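### Stage 2 combines the two arms for a reason that concerns response only and does not exempt safety, a co-primary outcome; the stage 1 toxicity tables are split by a dose cohort that the trial does not have

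*Protocol article*

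**What the plan says.** Under Statistical analysis, Stage 1, the DLT incidence is the main output, "which will be summarised by treatment arm (and within the high-and low-grade subtypes"). The next sentence covers baseline characteristics, dose delivery and all CTCAE toxicities, and uses a different grouping: these "during treatment will be summarised by grade and dose cohort".

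Under Statistical analysis, Stage 2, the rule is: "We do not expect a difference in response rates by arm, so for analyses, participants from arm A and arm B will be combined". The same paragraph rules out formal comparisons between groups, says that the arms exist mainly as a comparator for the translational endpoints, and defers detail to a statistical analysis plan.

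Other sections bear on this:

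- **Objectives and Endpoints:** safety and tolerability stand beside activity in the primary objective, and the endpoints are called co-primary.
- **Treatment arms:** both arms receive rituximab 375 mg/m² and varlilumab 3 mg/kg. The first varlilumab dose is on day 2 in arm A and on day 8 in arm B.
- **Stage 1 – safety:** each arm is cleared or stopped on its own DLT count.
- **Stage 2 – activity, safety and feasibility:** "In both stages, no dose reductions are allowed for rituximab or varlilumab". The section gives further safety information in a larger sample as an aim, and makes a future controlled trial conditional: "If these two experimental arms are shown to be active and safe".

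**The concern.** The premise of the pooling sentence is about response, but its conclusion covers analyses in general. Equal expected response gives no reason to pool toxicity. The one difference between the arms is how soon varlilumab follows rituximab in cycle 1, and that could affect early events. Infusion-related reactions and cytokine release syndrome are both on the protocol's own DLT list.

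If the sentence is followed as written, an imbalance in early toxicity between the two schedules would be averaged out in the final tables. A statement that both arms are safe would then rest, arm by arm, on the stage 1 participants alone. The term *dose cohort* adds doubt, because it leaves unclear whether even the stage 1 toxicity tables are split by arm.

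**Working it through.** **1. Is there a dose cohort?** Rituximab is 375 mg/m² in both arms, varlilumab is 3 mg/kg in both arms, and reductions are not allowed. That is one dose level per drug, so a table split by dose level would have a single column. Elsewhere the article uses cohort for the group within an arm: under Stage 1 – safety, an arm with one or two DLTs in three will "expand the cohort to three more participants". The likely meaning is therefore treatment arm, the grouping already used for DLT in the sentence before.

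**2. Numbers per arm.** At the start, "six participants (three from each arm and from any subtype) will be treated", so 2 × 3 = 6. If both arms expand, 2 × (3 + 3) = 12. This reproduces the stated range: "the number of patients recruited into stage 1 of the trial will range from 6 to 12". Stage 1 therefore holds 3 to 6 participants per arm. At full recruitment there are 10 per arm and grade, so 2 × 10 = 20 per arm and 40 in all, if both arms stay open.

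**3. What each sample can say about an event rate.** I use exact (Clopper-Pearson) 90% intervals, since 90% is the level the protocol chose. With zero events in n the upper limit is 1 − 0.05^(1/n).

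| Events / n | Where it arises | Exact 90% interval |
|---|---|---|
| 0/3 | an arm that proceeds without expansion | 0 to 63% |
| 2/6 | most events with which an expanded arm proceeds | 6% to 73% |
| 0/20 | full arm, zero events | 0 to 14% |
| 4/20 | full arm, assumed count | 7% to 40% |

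**4. What pooling would hide.** These counts are assumed, for illustration only.

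| | Events / n | Rate | Exact 90% interval |
|---|---|---|---|
| One arm | 6/20 | 30% | 14% to 51% |
| Other arm | 2/20 | 10% | 2% to 28% |
| Pooled | 8/40 | 20% | 10% to 33% |

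A pooled table shows only the last row.

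**5. Length of the DLT window.** Under Definition of DLT, the window opens at the first varlilumab dose and closes on day 1 of cycle 2. A cycle is 2 weeks, so without delay cycle 2 starts on day 15.

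- Arm A: 15 − 2 = 13 days.
- Arm B: 15 − 8 = 7 days.

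A delay to cycle 2 lengthens both windows. Arm A is observed for almost twice as long (13/7 ≈ 1.9), so raw DLT proportions by arm are not like for like.

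**The case against.** The strongest case on the other side has four parts.

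- **The pooling sentence is about response.** It opens with response rates and fits the sample size, which is set with the arms combined. It cannot cover every analysis, because the same paragraph keeps the arms apart for the translational endpoints. This makes a response-only intention plausible. However, the paragraph names the translational exception and names none for safety, so the text does not say so.
- **The detail belongs elsewhere.** A statistical analysis plan is to follow, and stage 2 safety analyses are to be agreed with the data monitoring and ethics committee. Table layout can indeed wait. But the article already states a pooling rule, and neither clause limits it.
- **Safety is a question about the combination.** The primary objective and the Discussion speak of combined therapy, and the remark about both arms is a condition for a later trial. That lowers the stakes, but stage 1 still decides arm by arm.
- **Tables by arm will be imprecise.** The assumed 6/20 against 2/20 gives a two-sided Fisher p of about 0.24. This supports describing without testing, and is no reason to leave the columns out.

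A reader might also infer more than the article supports:

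- *That stage 2 abandons DLT.* The stage 2 text is only silent. DLT is named in stage 1 because it is the gate there, and its definition is not confined to stage 1 participants.
- *That the stage 1 toxicity tables merge the arms.* A split by a variable with one level would be pointless, so loose wording is the better explanation.
- *That all 40 participants share one DLT window.* They do not, as step 5 shows.

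**Conclusion.** The point stands as a wording fault with a practical consequence. Read literally, the stage 2 rule pools a co-primary outcome for a reason that does not apply to it, and the stage 1 toxicity sentence names a grouping that does not exist. It is not shown that the trial team intends to withhold safety by arm: no sentence says that, and the monitoring committee's analyses are left open.

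The size is a matter of precision and visibility. By arm, the text secures safety summaries on 3 to 6 participants (upper limit 63% after 0/3), where up to 20 are available (14% after 0/20). A 20-point difference such as 30% against 10% would not be visible in the pooled figure.

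This assumes that both arms stay open and fill to 20. If one arm closes in stage 1, later recruits all enter the other arm and the question largely falls away. The 4/20, 6/20 and 2/20 counts are illustrations, not forecasts. The window lengths assume that cycle 2 starts on time.

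**What to change.** 1. In the stage 1 analysis, write treatment arm for *dose cohort*.
2. In the stage 2 analysis, limit the combining of arms to response and other activity endpoints.
3. State that CTCAE toxicity, DLT-defining events in cycle 1 and dose delivery will be summarised by arm as well as overall, for all treated participants from both stages, with 90% intervals for proportions and no formal comparison.
4. In the tables by arm, give the length of the DLT window (about 13 and 7 days without delay), and also show cycle 1 events over a common period. Two candidates are the whole of cycle 1 from day 1, and the first 7 days after the first varlilumab dose. The first has equal length but includes days before varlilumab, more of them in arm B. The second aligns the arms on time since varlilumab. This concerns reporting only and leaves the DLT definition and the stage 1 rules as they are.

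The cost is a few sentences and some extra table columns with small numbers per arm. No new data should be needed, because adverse events are already graded and attributed at each treatment cycle.
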